## Abstract

**Background:**

Integrative medicine (IM) provides patient-centered care and addresses the full range of physical, emotional, mental, social, spiritual, and environmental influences that affect a person’s health. IM is a “whole systems” approach that employs multiple modalities as opposed to an isolated complementary therapy. Thus, studying outcomes of IM is more challenging than evaluating an isolated intervention. Practice-based research networks (PBRNs) allow for clinicians/investigators at multiple diverse sites using common methodology to pool their data, increase participant sample size and increase generalizability of results. To conduct real-world, practice-based research, the Bravewell Collaborative founded BraveNet in 2007 as the first national integrative medicine PBRN.

**Methods and design:**

Patients Receiving Integrative Medicine Effectiveness Registry (PRIMIER) is a prospective, non-randomized, observational evaluation conducted at fourteen clinical sites. Participants receive a non-standardized, personalized, multimodal IM approach for various medical conditions. Using the REDCap electronic platform, an anticipated 10,000 study participants will complete patient-reported outcome measures including Patient Reported Outcomes Measurement Information System (PROMIS)-29, Perceived Stress Scale-4, and the Patient Activation Measure at baseline, 2, 4, 6, 12, 18 and 24 months. Extractions from participants’ electronic health records include IM services received, as well as ICD diagnostic codes, and CPT billing codes associated with each IM visit. Repeated-measures analyses will be performed on data to assess change from baseline through 24 months with planned subgroup analyses to include specific clinical population and specific IM intervention or combinations.

**Discussion:**

As the PRIMIER registry grows, we anticipate that our results would provide an indication of the promise of PBRN research efforts in IM. Analyses will incorporate a large sample of participants and an expected 10-year observation period and will provide the ability to evaluate the effect of IM on outcomes for specific clinical populations and specific IM interventions or combinations. As such, PRIMIER will serve as a national platform for future evaluations of IM best practices.

**Trial registration:**

Clinical Trials.gov NCT01754038

**Electronic supplementary material:**

The online version of this article (doi:10.1186/s12906-016-1025-0) contains supplementary material, which is available to authorized users.

## Background

Integrative medicine (IM) provides patient-centered care and addresses the full range of physical, emotional, mental, social, spiritual, and environmental influences that affect a person’s health [1]. Employing a personalized strategy that considers the patient’s unique conditions, needs, and circumstances, IM uses the most appropriate interventions from an array of scientific disciplines to heal illness and help people regain and maintain optimal health [1]. Because IM is a “whole systems” approach that employs multiple modalities in concert as opposed to an isolated complementary therapy, studying outcomes is more challenging than evaluating an isolated pharmaceutical or botanical intervention [2].

“Patient-reported outcome” (PRO) measures are health data provided directly by patients, rather than outcomes that reflect the assessment of an investigator or clinician, as typically seen in clinical research. A PRO is an individual patient’s self-reported assessment of their feelings or functions as they are dealing with diseases or conditions, and this assessment has important implications both in clinical practice and in research. PRO data are especially important in evaluating the effectiveness of health care for chronic conditions, where a primary goal of treatment is to improve patients’ function and to reduce symptoms associated with the condition [3, 4]. Criticisms of the use of PROs in clinical research have been the wide range of instruments used, often to measure similar outcomes, and the lack of standardization between outcome measures [4]. The recent development [5] of the NIH-funded Patient-Reported Outcomes Measurement Information System (PROMIS) suite of item banks and short forms for assessing health outcome domains related to quality of life and chronic conditions has been cited by researchers as a viable solution to these concerns [4, 6].

Single-site studies in IM are generally too small to identify differences in outcomes across sociodemographic or clinical subgroups. Multi-institutional scientific networks are able to recruit large numbers of participants for observational and interventional trials. Practice-based research networks (PBRNs) allow for clinicians/investigators at multiple diverse sites using common methodology and a single coordinating/data analysis center to pool their data as well as increase generalizability of results. By collecting data in the context of patients receiving their clinical care, the results are more reflective of “real world” outcomes. Given the growth of the number of clinics providing IM [7] and the resulting need for these clinics to conduct real-world, practice-based research, the Bravewell Collaborative founded BraveNet in 2007 as the first national IM PBRN. BraveNet, a registered PBRN with the Agency for Healthcare Research and Quality (AHRQ), was established with the intent that it would provide data on IM’s use, effectiveness, safety, costs, and patient satisfaction. As of early 2015, BraveNet consists of 14 IM clinics that have robust patient populations as well as strong research capabilities.

In this description of our study protocol, we describe the approach taken to conduct a multi-site prospective observational cohort study of PROs in our network of IM clinics. The Patients Receiving Integrative Medicine Interventions Effectiveness Registry (PRIMIER) provides an opportunity to better understand which IM interventions patients are receiving, and how these interventions impact both clinical measures and PROs, such as quality of life. Because randomized controlled trials can only examine one or two specific interventions for a narrowly defined condition—and because IM often uses highly individualized combinations of interventions to treat multiple conditions simultaneously—the evidence base to support clinical decision making in IM is not progressing rapidly enough to address the widespread use of this approach in our health care system [8]. There have been a few attempts to conduct randomized trials of IM interventions. However, these have been limited by: small sample size and inadequate power [9]; generalizability and resource intensiveness [10]; and retention challenges potentially related to participant dissatisfaction with being randomized to the non-IM arm, as well as limited follow-up [11].

## Methods

### Overview

In 2013, BraveNet created and launched PRIMIER (Patients Receiving Integrative Medicine Interventions Effectiveness Registry), a multi-institutional project designed to uniformly collect PROs and extract electronic health record (EHR) data into a large national registry. The goal of PRIMIER is to provide a framework that can be used for evidence-based practice, discernment of best practices of IM, and quality improvement. PRIMIER is listed in the Registry of Registries (RoPR ID: 40), which is maintained by AHRQ and ClinicalTrials.gov (NCT01754038). The intent is that PRIMIER will continue to expand over time, including more publicly-funded as well as private IM centers with ever increasing data which could be used for the mentioned objectives. At present, PRIMIER is 2 years into an anticipated 10-year study timeframe. Active enrolling sites are expected to grow significantly beyond the present 14 recruiting centers.

### Research setting and eligibility criteria

As of June 30, 2015, the BraveNet PBRN includes the 14 member sites listed in Table 1 as well as the BraveNet Data and Statistical Coordinating Center. Most of our sites are specialty care, integrative medicine clinics, although an increasing number of member clinics have primary care capacities. The study is open to any patient age 18 or over who is seen by a provider for clinical purposes at any of the sites. Study participants must be willing and able to provide informed consent, to participate, and to be contacted in the future by study personnel. Patients who are involved only in an education program or one-time activity are excluded from participation.

**Table 1 Tab1:** BraveNet Member Clinics (as of 6/30/2015)

Site	Location
Alliance Institute for Integrative Medicine	Cincinnati, OH
Boston Medical Center at Boston University	Boston, MA
Center for Integrative Medicine at University of Maryland School of Medicine	Baltimore, MA
Duke Integrative Medicine at Duke University	Durham, NC
Integrative Medicine at the University of Colorado Denver	Denver, CO
Jefferson-Myrna Brind Center for Integrative Medicine at Thomas Jefferson Medical College	Philadelphia, PA
Mount Sinai Beth Israel Center for Health and Healing	New York, NY
Osher Center for Integrative Medicine at Northwestern University	Chicago, IL
Osher Center for Integrative Medicine at University of California, San Francisco	San Francisco, CA
Osher Center for Integrative Medicine at Vanderbilt University	Nashville, TN
Penny George Institute for Health and Healing at Allina Health	Minneapolis, MN
Scripps Center for Integrative Medicine at Scripps Health	La Jolla, CA
Simms/Mann Health and Wellness Center, Program in Integrative Medicine at Venice Family Clinic	Los Angeles, CA
University of Pittsburgh Center for Integrative Medicine	Pittsburgh, PA

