### Screening procedures and enrollment

Potential participants receive PRIMIER enrollment information either from clinic or research staff. Patients who decide to participate in PRIMIER log onto the PRIMIER website and electronically enroll directly into the registry. Online registrants are able to provide informed consent upon opening the first screen on their initial visit to the website. If they do not have computer access or are uncomfortable with technology, patients may provide informed consent and complete the survey questionnaire by pen and paper. Following enrollment in PRIMIER, PRO measures are obtained at 2-month intervals for the first 6 months, then every 6 months through the end of year two. This information is combined with data extracted from the participants’ EHR. We anticipate approximately 10,000 participants to be enrolled in PRIMIER.

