### Utilization/intervention data

In addition to providing PRO measures, participants report the primary condition(s) or symptom(s) for which they are receiving treatment and the type of IM practitioner from whom they are receiving care based on questions from the National Health Interview Survey. At each data collection point, patients are asked to rate or describe their change in symptoms, etc. since beginning care at the IM clinic [27]. Patients report whether they are experiencing chronic pain, defined as 4 or greater on an 11-point visual analog scale. PRIMIER also collects information on what IM interventions patients have utilized in the past 6 months. Utilization of IM treatments is captured through two methods: 1) as reported by the study participants using patient visit questionnaires; and 2) as reported by the sites through an electronic or paper medical record extraction process. Each site abstracts the following data points from their participant’s electronic medical and administrative records: dates of all appointments to the IM clinic, IM services received, diagnostic codes (International Classification of Diseases-9: ICD-9) associated with each IM visit, and billing codes (Current Procedural Terminology: CPT) associated with each visit. These data are encrypted and sent electronically to the BraveNet data coordinating center. Additional data fields will be added from patient visits to any clinic (i.e., not limited to IM clinic visits) as relevant to specific studies of interest, for example, height, weight, pain, and lipid panels.

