As our sample size increases and the proportion of those completing long term follow-up assessments grows, we will be able to evaluate the impact of IM on pain scores in subgroups including but not limited to: sex, BMI < 30 vs BMI ≥ 30, and <40 on the PROMIS Depression Subscale vs ≥40 on PROMIS Depression Subscale. The potential of the varying impacts of IM on subgroups will be assessed by including interaction terms, i.e., subgroup by IM, in the MSM model. In the case that the interaction terms are statistically significant, separate MSM analyses will be performed within each subgroup. Also, the weight estimates for each subject visit will be computed adjusting for dose of modality or modalities of interest (e.g., acupuncture or IM physician visit) instead of IM modality in the MSM analysis. Accounting for modality dosing by visit over the course of the study may potentially create more robust weight estimates for each subject by providing more information than just a binary response variable.

Sensitivity analysis to assess the impact of retention rate will be performed on pre-specified subgroups of subjects who completed:75 % of surveys over the study period50 % of surveys over the study period25 % of surveys over the study period

All analyses will be conducted using SAS (Cary, NC).

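### Baseline is not tied to the start of integrative medicine (IM) care and no non-IM comparator is described, so pooled change from baseline cannot by itself support claims about the effect of IM

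*Protocol article*

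**What the plan says.** - **Eligibility.** Under Research setting and eligibility criteria the study is "open to any patient age 18 or over who is seen by a provider for clinical purposes" at a member site. Apart from consent and willingness to take part, the only restriction is this: "Patients who are involved only in an education program or one-time activity are excluded from participation". Prior IM care is neither required nor excluded.
- **Time zero.** Screening procedures and enrollment states: "Following enrollment in PRIMIER, PRO measures are obtained at 2-month intervals for the first 6 months". Nothing says where in a course of care enrolment falls.
- **Content of the baseline survey.** Utilization/intervention data says that at every collection point "patients are asked to rate or describe their change in symptoms, etc. since beginning care at the IM clinic". Table 2 marks this item at baseline, together with self-reported IM use and IM clinic appointment dates. Participants are also asked about IM use over the previous 6 months.
- **Exposure.** The abstract describes participants as receiving a personalised, multimodal IM approach. No group without IM is described anywhere.
- **Analysis.** The abstract states: "Repeated-measures analyses will be performed on data to assess change from baseline through 24 months". Future data analysis adds a marginal structural model (MSM) whose exposure is a pre-chosen IM modality or set of modalities, tracked over time. Subgroup differences are to be assessed by "including interaction terms, i.e., subgroup by IM, in the MSM model", with modality dose as an alternative basis for the weights.
- **Claims.** The abstract's discussion says the analyses "will provide the ability to evaluate the effect of IM on outcomes for specific clinical populations". Future data analysis sets out to evaluate the impact of IM on pain scores by subgroup.

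**The concern.** Two features combine. First, if some participants are already in IM care when they enrol, their baseline is an on-treatment value, and change from that point measures something different from change after starting care. Second, with no non-IM group, nothing separates an IM effect from what would have happened anyway. People who enter care when their symptoms are bad tend to score better later, with or without treatment.

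Pooled change then depends partly on the mix of new and established enrolees. A subgroup with more new patients could show more change for that reason alone, and this could be reported as a larger impact of IM. At the anticipated enrolment of about 10,000, random error is small, so such artefacts would look precise.

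**Working it through.** The article gives no sample-size calculation, SD, retest correlation or share of established patients, so there is no plan figure to reproduce. Steps 2 and 3 use assumed inputs and show ranges only.

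**1. Can baseline fall after the start of care?** The eligibility rule has no first-visit condition, and the clock starts at registry enrolment. The symptom-change item refers to the period "change in symptoms, etc. since beginning care at the IM clinic" and is asked at baseline. It is informative there only for someone whose care has begun. Together these admit both kinds of patient. None of the analyses described in the abstract, General statistical considerations or Future data analysis splits or adjusts by prior IM care.

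**2. What does pooled change estimate?** Let E be the true IM effect, p the share of established patients, f the fraction of E already realised before enrolment in those patients, and D the change expected without IM (taken as equal in both groups for simplicity). Then

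pooled change = D + E × (1 − p × f).

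With E = 3 points assumed:

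| D | p | f | Pooled change |
|---|---|---|---|
| 0 | 0 | – | 3.0 |
| 0 | 0.5 | 1 | 3 × 0.5 = 1.5 |
| 0 | 1 | 1 | 0 |
| 2.5 | 0.5 | 1 | 2.5 + 1.5 = 4.0 |
| 2.5 | 0 | – | 2.5 + 3 = 5.5 |

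The same true effect can appear as anything from 0 to 5.5, so the bias can go either way.

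**3. How large could regression to the mean be?** Suppose mean scores at enrolment lie d points on the worse side of the long-run population mean and the retest correlation is r. The expected return is d × (1 − r). The standard error of mean change is SD × √(2(1 − r)) / √N. Assume SD 10, d from 5 to 10 and r from 0.5 to 0.8, with N = 10,000:

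- Smallest: 5 × (1 − 0.8) = 1.0 point; SE = 10 × √0.4 / 100 = 0.063; ratio about 16.
- Largest: 10 × (1 − 0.5) = 5.0 points; SE = 10 × √1 / 100 = 0.10; ratio 50.

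The formula applies to distance from the population mean. A patient temporarily above their own usual level would be expected to return the whole way.

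**4. What can the interaction estimate?** Take the columns intercept, subgroup, IM and subgroup × IM.

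- If IM means any IM, it equals 1 for everyone. The third column then repeats the first and the fourth repeats the second. The rank is 2 of 4, and neither IM term is estimable.
- If IM means a modality flag m, the rank is 4 of 4. Write mean change as E + a_s + b_s × m in subgroup s. The modality contrast is b_s and the interaction is b_1 − b_0. E cancels from both.

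A simulation of 10,000 subjects agrees. Setting E to 0, 3 and 6 points of score reduction moved the fitted intercept to −0.17, −3.13 and −5.82. So the whole-system effect goes into the intercept, and the term compares one modality with other IM care.

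**The case against.** The strongest reply is that the article's causal analysis is the MSM and not the pooled change. Its exposure is a chosen modality. The interaction sits inside that model, and the next step replaces modality by dose, so IM there is most naturally shorthand for the modality. The abstract sentence about the effect of IM goes on to name particular interventions and combinations. The Discussion gives examples such as more versus less frequent acupuncture. All of this stands. A reader might infer that the subgroup-by-IM term has no contrast at all. The documents do not support that: it has a workable reading, and the fault lies in the wording and the estimand.

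A reader might also infer that patients enrolled after years of care, or that early non-responders had already left. The text says neither. It only leaves room for both, and gives no share of established patients. Nor does earlier treatment invalidate the MSM through its effect on baseline covariates: a model of later modality use may condition on that history, and then estimates the effect of subsequent treatment given it.

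The article does acknowledge the lack of randomisation and the clinically driven make-up of the cohort, and describes some of its output as preliminary. A detailed covariate list may properly be left to an analysis plan. But the stated limitations do not name patients already in care, the missing non-IM comparator or regression to the mean. Weighting for modality choice cannot supply an untreated comparison.

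**Conclusion.** The point holds in this form. Baseline is not anchored to the start of IM care, so the cohort can mix new and established patients, and the stated analyses do not separate them. With no non-IM comparator, pooled change from baseline cannot by itself support the effect of IM announced in the abstract or the impact of IM in Future data analysis. The MSM can support contrasts between a chosen modality, or its dose, and other IM care, subject to its usual assumptions.

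The size is unknown. The 1 to 5 points of regression to the mean and the 0 to 5.5 range for a true 3-point effect rest on assumed values of SD, elevation at enrolment, retest correlation and prior exposure. They show that the bias could match a plausible effect and far exceed sampling error, and they are not estimates for this registry.

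**What to change.** 1. Classify each participant as new or established at baseline from the IM clinic appointment dates already extracted. Where records do not reach the first visit, use reported IM use in the past 6 months as a check.
2. Report change from baseline separately for the two groups. Making new patients the main set is a matter of preference in an all-comers registry and is not required.
3. Include prior IM exposure in the MSM treatment-weight model.
4. In Future data analysis, replace the subgroup-by-IM term with subgroup by modality (or modality dose), and name the comparator.
5. State, in the abstract as well, that change from baseline is descriptive and that effect claims are limited to between-modality or dose contrasts.

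The cost is analysis-plan and abstract wording, with no new data collection. The price is smaller strata and a more modest claim.

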### Ethics, consent and permissions

All participants will be asked to provide informed consent before initiation of any study-related procedures. The protocol was approved by the Institutional Review Board at each participating site including Beth Israel Medical Center Human Subjects Protection Office Institutional Review Board; Boston University Medical Center Institutional Review Board; Colorado Multiple Institutional Review Board; Duke University Health Systems Institutional Review Board; Northwestern University Institutional Review Board; Schulman Associates Institutional Review Board; Scripps Clinic Institutional Review Board; Thomas Jefferson University Division of Human Subjects Protection; University of California Los Angeles Institutional Review Board; University of California San Francisco Committee on Human Research; University of Maryland Institutional Review Board; University of Maryland Institutional Review Board and Vanderbilt University Human Research Protection Program. In addition, the Einstein Human Research Protection Program and Duke University Health Systems Institutional Review Board approved the study as the BraveNet Data and Statistical Coordinating Center. The study is registered in Clinical Trials.gov (NCT01754038).

### Screening procedures and enrollment

Potential participants receive PRIMIER enrollment information either from clinic or research staff. Patients who decide to participate in PRIMIER log onto the PRIMIER website and electronically enroll directly into the registry. Online registrants are able to provide informed consent upon opening the first screen on their initial visit to the website. If they do not have computer access or are uncomfortable with technology, patients may provide informed consent and complete the survey questionnaire by pen and paper. Following enrollment in PRIMIER, PRO measures are obtained at 2-month intervals for the first 6 months, then every 6 months through the end of year two. This information is combined with data extracted from the participants’ EHR. We anticipate approximately 10,000 participants to be enrolled in PRIMIER.

